## Methods/design

### Study design

DETECTOR project is a multicentric prospective cohort study, funded by the French National Cancer Institute, the National League against Cancer and the Foundation for Cancer Research, in a collaborative effort of Paris Descartes University associated hospitals and Paris Diderot University. This trial intends to evaluate unenhanced LDCT in combination with the detection of CTC, in the screening of smoking-associated cancers in patients with PAD or AAA as well as the psychological impact of this screening strategy.

After inclusion in the trial, participants will undergo the first round of screening. Participants without prevalent cancer at baseline will undergo two other screening rounds at one-year interval each, combining LDCT and CTC search on a blood sample (Table 1). Participants will be followed for a total of at least 3 years after inclusion.

**Table 1 Tab1:** Study flow chart of examinations

Actions	V0: baseline visit	within 1 m after V0	V0 + 5w	V1(V0 + 1y)	V1 + 5w	V2(V0 + 2y)	V2 + 5w
Information	✓						
Informed consent	✓						
Verification of inclusion and exclusion criteria	✓						
Enrolment	✓						
Psychologist presence^(1)^	✓						
Personal and family medical history^(2)^	✓						
Ongoing treatments	✓			✓		✓	
Socio-demography	✓						
Level of tobacco use	✓						
Screening round: - Blood sampling for CTC detection - LDCT	✓			✓		✓	
Results of the screening round			✓		✓		✓
Psychological counselling^(3)^		✓	✓	✓			
Clinical events since last visit^(2)^				✓		✓	
Adverse events	✓		✓	✓	✓	✓	✓

1: as an observer; 2: focused on cancer and vascular diseases; 3: only for patients who are volunteer to participate at the psychological study

The study sponsor is Paris Saint-Joseph Hospital. The study was registered in the French National Agency for Medicines and Health Products Safety (No N° EUDRACT_ID RCB: 2016-A00657–44) and was approved by the ethics Committee for Persons Protection (Comité de Protection des Personnes Ile de France II, IRB number 1072 and n° initial agreement 2016-08-02). The total duration of the trial is 6 years (inclusion period = 36 months; follow-up = 3 years; ClinicalTrials.gov identifier NCT02849041). Prolonged follow-up of trial participants will be performed each year after the end of the scheduled trial period. The first study participant has been enrolled on January 2017; last patient’s enrollment is expected on December 2019.

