### Objectives

The primary objective of the study is to determine the diagnostic value of the couple LDCT combined with CTC search for the early detection of smoking associated cancers in a cohort of asymptomatic but high-risk participants presenting with PAD and/or AAA.

The secondary objectives are (1) to describe detected malignancies with this screening strategy and to evaluate patient’s survival, (2) to evaluate the rate of detection of CTCs in the study population, (3) to study the effect of smoking cessation program on patient’s decision to quit smoking, (4) to study the emotional and psychosocial impact of this screening strategy and more specifically related to CTC detection, (5) to assess, adjust and improve communication strategies of health professionals.

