### Statistical analysis and sample size

Data will be analyzed using SAS and R software. Alpha level for statistical significance (p) will be set at less than 5%. Characteristics of the study population will be described as mean plus or minus standard deviation for continuous variables with a normal distribution and as median [interquartile range] for skewness distribution. Categorical variables will be described as numbers and proportions. Student’s t-test or nonparametric Wilcoxon test will be used to compare quantitative parameters between different groups of patients and Chi2 test or Fischer test for qualitative parameters.

The primary outcome will focus on the sensibility and specificity of the screening strategy associating detection of CTCs and LDCT. Statistical analysis is in accordance with the STARD (Standards for Reporting of Diagnostic Accuracy Studies) guidelines [24]. To meet the primary objective, sensitivity will be estimated by dividing the number of patients diagnosed by the CTC method by the number of patients with lung cancer confirmed by the reference technique, i.e. LDCT. The results will be expressed with a binomial proportion 95% confidence interval. Specificity will be estimated by dividing the number of patients diagnosed with CTC as cancer-free with the number of patients without lung cancer. Secondary evaluation criteria will be analyzed using the same statistical methods as those used for the primary endpoint.

Assuming 10% prevalence of smoking-associated cancer in the studied population [8], if we aim to study a total of at least 30 detected cancers, including baseline and repeat screening rounds, we need to enroll a total of at least 300 participants.

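### The rule that sends all secondary criteria to the primary endpoint's methods does not fit survival, where a crude proportion alive among detected cancers would be biased by unequal follow-up

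*Protocol article*

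**What the plan says.** All references are to the protocol article.

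- **Statistical analysis and sample size, primary endpoint:** "The primary outcome will focus on the sensibility and specificity of the screening strategy associating detection of CTCs and LDCT". Sensitivity and specificity are each defined as one count of patients divided by another, and "The results will be expressed with a binomial proportion 95% confidence interval".
- **Same section, secondary criteria:** "Secondary evaluation criteria will be analyzed using the same statistical methods as those used for the primary endpoint". No exception is made. The only other procedures named there are descriptive summaries, the t-test, Wilcoxon, chi-squared and Fisher tests.
- **Objectives, first secondary objective:** "to describe detected malignancies with this screening strategy and to evaluate patient’s survival".
- **Study design, follow-up:** "Participants will be followed for a total of at least 3 years after inclusion". Also: "The total duration of the trial is 6 years (inclusion period = 36 months; follow-up = 3 years". Yearly follow-up continues after the scheduled end. Participants without cancer at baseline have two further screening rounds, one and two years after inclusion.

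**The concern.** A binomial proportion needs every patient's status at the same, fully observed time. Survival after a screen-detected cancer does not meet that condition here. Two patients who enter on the same day, one diagnosed at baseline and the other at the third round, differ by two years in how long they can be observed after diagnosis. Dividing the number alive by the number diagnosed treats them as equally observed.

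The figure would then depend on the mix of detection rounds and on when the database closes, as well as on survival. This matters because the study's rationale is to find cancers while they are still curable, so readers will look at the survival of detected cases even though it is a secondary objective.

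The concern is with a rule that the article states. Silence about the survival method would not have been a finding, since an article may leave that to the full protocol or analysis plan.

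**Working it through.** **Inputs from the article.** Rounds at years 0, 1 and 2; inclusion period 3 years; total duration 6 years; follow-up of at least 3 years; 10% prevalence; at least 30 cancers; at least 300 participants.

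**Assumptions (not in the article).** True 3-year survival from diagnosis S₃ of 30%, 50% or 70%; constant hazard λ = −ln(S₃)/3, the same for all rounds; diagnosis dated at the round; no loss to follow-up; cancers split across the three rounds in equal thirds or 60/20/20.

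**The plan's own figure.** 30 / 0.10 = 300, as stated. It does not depend on the survival method. The article gives no survival figure to reproduce.

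**Step 1: observation time after diagnosis.**

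| Round | (a) Follow-up stops 3 years after inclusion | (b) Common closing date at 6 years, uniform entry over 3 years |
|---|---|---|
| Baseline | 3 years | 3–6 years |
| Year 1 | 2 years | 2–5 years |
| Year 2 | 1 year | 1–4 years |

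**Step 2: expected crude proportion alive.** With w the share of cancers found at each round:

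- (a) sum of w · exp(−λf), with f = 3, 2, 1.
- (b) sum of w · [exp(−λl) − exp(−λ(l+3))] / (3λ), with l = 3, 2, 1.

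Example with S₃ = 50%, so λ = 0.231 per year, and equal thirds:

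- (a) (0.500 + 0.630 + 0.794)/3 = 0.641, which is 14.1 points too high.
- (b) (0.361 + 0.454 + 0.573)/3 = 0.463, which is 3.7 points too low.

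**Step 3: all scenarios.**

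| Split | True S₃ | (a) crude | error, points | (b) crude | error, points |
|---|---|---|---|---|---|
| Equal thirds | 30% | 47.3% | +17.3 | 27.5% | −2.5 |
| Equal thirds | 50% | 64.1% | +14.1 | 46.3% | −3.7 |
| Equal thirds | 70% | 79.2% | +9.2 | 66.6% | −3.4 |
| 60/20/20 | 30% | 40.4% | +10.4 | 23.5% | −6.5 |
| 60/20/20 | 50% | 58.5% | +8.5 | 42.2% | −7.8 |
| 60/20/20 | 70% | 75.5% | +5.5 | 63.5% | −6.5 |

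The sign changes with the closing rule.

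**Step 4: whole cohort from inclusion.** If status is taken at exactly 3 years and everyone is observed to then, the binomial proportion is unbiased. With 5% to 20% lost over 3 years and assumed 3-year survival of 70% to 90%, the error is about 0.2 to 3 points, whether the lost are counted as alive or left out. If status is instead taken at a common closing date, the crude proportion alive is 58.9%, 71.7% or 85.4% when 3-year survival is 70%, 80% or 90%. The problem is therefore small only if the 3-year landmark is fixed.

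**The case against.** **The sentence may be a loose catch-all.** The article never lists its secondary evaluation criteria, and the psychological objectives plainly have their own qualitative methods in the section Psychological study. The sentence thus has at least one evident exception, and survival may be another that the full protocol spells out. This stands in part: a reader might infer that a binomial survival analysis is firmly planned, and the article does not go that far. But survival is a named quantitative objective, the rule as written covers it, and nothing else in the section handles censoring.

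**Survival from inclusion is nearly safe.** Every participant is due at least 3 years of follow-up, so staggered entry causes no administrative censoring before that point. This stands. A reader might infer that every survival figure would be uninterpretable or would depend on accrual timing; for a 3-year proportion from inclusion with complete follow-up, that is not so. The article does not, however, fix this landmark or this time origin.

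**A larger artefact can be shown.** With an assumed hazard of 0.2 per year, the proportion dead is 1 − exp(−0.2) = 18% after 1 year and 1 − exp(−0.6) = 45% after 3 years. A reader might take the 27-point gap as the size of the problem. It contrasts third-round with baseline cancers, a comparison the article does not plan, and it assumes a hazard and follow-up that stops at 3 years. The pooled errors above are the fairer measure.

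**Vascular death as a competing risk.** The objective concerns patient survival, for which a vascular death is an event. A competing-risk analysis of cancer death would add an endpoint; its absence is not an error.

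**Limited weight.** Survival is one clause of a secondary objective in a cohort expecting about 30 cancers. With 15 of 30 alive, the exact 95% interval is already 31% to 69%. That is fair, but wide intervals do not excuse centring them on the wrong quantity.

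**Conclusion.** The concern holds for survival, chiefly survival after diagnosis. The article assigns all secondary criteria a method that takes no account of differing observation time, and one of its named secondary objectives needs a method that does. Under the stated assumptions, a pooled crude proportion alive would overstate 3-year survival from diagnosis by about 5.5 to 17.3 points if follow-up stops 3 years after inclusion, and understate it by about 2.5 to 7.8 points with a common closing date. The survival levels, the constant hazard and the split across rounds are illustrative. What does not depend on their exact values is that time after diagnosis differs by round.

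The rule suits the secondary criteria that are true proportions, such as the CTC detection rate. The primary endpoint and the figure of 300 participants are untouched. This is a clear mismatch in a secondary analysis, worth correcting because the correction is so cheap.

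**What to change.** Limit the sentence to the secondary criteria that are proportions, for example the CTC detection rate and the quit rate, which keep a binomial 95% confidence interval. Then add that overall survival will be estimated by Kaplan-Meier with 95% confidence intervals:

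- from inclusion for all participants;
- from diagnosis for participants with a detected cancer;
- with participants not known to have died censored at last contact.

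Label survival from diagnosis as descriptive. It includes lead time, and because censoring is tied to the detection round, the pooled curve also relies on prognosis being similar across rounds. A competing-risk analysis of cancer death is optional and is not needed for this correction.

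The cost is one or two sentences and a routine analysis. The sample size does not change. Since follow-up is already planned, little or no extra data should be needed beyond dates of inclusion, diagnosis, death and last contact.

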### Study population

From January 2017, patients consulting for PAD or AAA in the departments of vascular medicine or surgery in Paris Saint-Joseph Hospital and European Georges Pompidou Hospital will be consecutively included after signed informed consent. Eligible participants, affiliated to the French social security system, are between 55 and 80 years of age at the time of inclusion, have a history of cigarette smoking of at least 30 pack-years, and, if former smokers, have quit within the previous 15 years. Active smoking patients at the time of inclusion in the study must engage in smoking cessation. Peripheral arterial disease is defined according to the following criteria: asymptomatic patients with ankle-brachial pressure index value less than 0.90 or pulse abolition with imaging-documented atherosclerotic vascular disease; symptomatic patients with intermittent claudication or chronic ischemic rest pain with or without tissue loss; acute limb ischemia; presence of AAA, defined as a localized dilation of the aorta of at least 50% in relation to the normal adjacent aorta measured by duplex-ultrasound or CT-scan.; previous arterial revascularization procedure of lower limb (by angioplasty or surgery) or amputation due to PAD.

Exclusion criteria are treatment for, or evidence of, any cancer within 5 years before enrollment, except non-melanoma skin cancer and in situ carcinomas, previous lung resection surgery, acute respiratory tract infection treated with antibiotics in the previous 12 weeks, contraindication to any invasive thoracic procedure, any sign suggestive of prevalent malignancy (unexplained weight loss ≥10% in the previous 12 months, recent hemoptysis…), renal insufficiency (creatinine clearance < 30 ml/mn) not allowing - if appropriate - injection of contrast medium, psychiatric comorbidities or limited life expectancy due to concomitant disease, ECOG Performance Status ≥2.

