Repetition of screening examinations raises the question of the risks associated with low-dose but repeated diagnostic irradiations. Irradiation delivered by a LDCT or a PET scanner is not negligible (1.5 mSv for LDCT) and may cause an excess risk of cancer. However, this risk appears much lower than the number of spontaneous cancers observed in a population at risk, which justifies the completion of these examinations [31]. In the NLST study, a positive examination was defined by the presence of at least one non-calcified nodule larger than or equal to 4 mm which led to a 27% positive test rate, 96% of which were false positives. We chose to apply the criteria of the NELSON study which demonstrated a significant reduction of false positive rate.

Common risk factors and pathophysiological processes have been highlighted in cancer and atherosclerosis, involving genetic alterations, inflammatory pathways, uncontrolled cell proliferation and pro-thrombotic processes [32]. Secondary cardiovascular prevention measures help delay vascular related events in PAD patients whereas epidemiological data underline an increase incidence in cancer and related death in the follow-up, compared with the general population, particularly for tobacco-related cancers [33, 34]. Large data from population-based cohort studies highlighted a 40% increased risk for cancer among patients with intermittent claudication [34, 35]. Prospective data reported a prevalence of 11.5% for malignancies in patients with critical leg ischemia and half of this population had died within 6 months [8]. However, not all of the patients with critical leg ischemia were investigated for occult malignancy, but only those with suggestive symptoms. The true prevalence of occult cancer in this population could thus be higher. The clinical benefit of a special workup for neoplasms in patients with PAD and a history of cigarette smoking has never been investigated. Furthermore, most patients diagnosed with cancer in the follow-up after PAD treatment exhibited advanced stage and poor survival [11, 34]. The clinical benefit of early cancer detection in this population may thus be expected. Although the lung is particularly susceptible for tobacco-induced cancer, a screening strategy should also have the potential to detect early stage neoplasm in all target organs. Circulating tumor cell search in the peripheral blood may represent a reliable tool suggestive for occult cancer in high risk PAD patients [18].

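### The 300 participants correspond to about 30 cancers expected to be present, not to at least 30 detected, and the 30 covers all smoking-associated sites while the sensitivity denominator is lung cancer only

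*Protocol article*

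**What the plan says.** All of the sizing stands in one sentence of the protocol article, under Statistical analysis and sample size. It assumes a 10% prevalence of smoking-associated cancer, attributed to reference 8. It then reasons that "if we aim to study a total of at least 30 detected cancers, including baseline and repeat screening rounds, we need to enroll" 300 people or more.

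Four other places bear on it:

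- **Same section, primary outcome.** Sensitivity is the number of patients diagnosed by the CTC method divided by "the number of patients with lung cancer confirmed by the reference technique", which is named as LDCT. Specificity is likewise taken over patients without lung cancer.
- **Objectives.** The primary objective concerns smoking-associated cancers in general, not lung cancer alone.
- **Discussion.** Reference 8 is described as reporting a "prevalence of 11.5% for malignancies in patients with critical leg ischemia and half of this population had died within 6 months". Not all of those patients were worked up for occult malignancy, "but only those with suggestive symptoms". The article then notes that the true prevalence of occult cancer could be higher.
- **Study population.** The exclusions include "any sign suggestive of prevalent malignancy", cancer within 5 years (with exceptions for non-melanoma skin cancer and in situ carcinomas) and limited life expectancy. Eligible patients range from asymptomatic PAD and claudication to rest pain with or without tissue loss, acute limb ischaemia and AAA.

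**The concern.** A prevalence multiplied by a sample size gives the expected number of cancers present. The target, however, is worded as a minimum number detected. Moving from one to the other needs an assumption about how many cancers the programme finds and how many participants stay for all rounds, and the sentence uses neither. It also applies a figure called a prevalence to baseline plus two repeat rounds, which mixes cancers present at entry with cancers that arise later.

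The condition counted also changes within the section: the sizing counts all smoking-associated cancers, while the accuracy formula counts lung cancers. A reader will take 30 as the case number behind the primary sensitivity estimate and credit that estimate with more precision than the design is likely to give.

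**Working it through.** **Inputs from the protocol article.** Prevalence 10%; target at least 30 detected; N at least 300; source figure 11.5%; 95% binomial interval for sensitivity.

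**Assumed inputs.** The article does not give the share of cancers detected (s), the lung share, or a frequency other than 10% and 11.5%. Ranges are shown for each.

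**1. Reproducing the plan's figure.** 30 / 0.10 = 300, an exact match. No other input is needed, so the figure implies s = 1 and no loss.

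**2. Chance of at least 30 detected among 300.** The number detected is taken as Binomial(300, p × s), with no loss.

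| Frequency p | Detected share s | Expected detected, 300 × p × s | P(at least 30) | N for an expected 30, 30/(p × s) |
|---|---|---|---|---|
| 10% | 100% | 30 | 0.53 | 300 |
| 10% | 90% | 27 | 0.30 | 334 |
| 10% | 80% | 24 | 0.12 | 375 |
| 10% | 70% | 21 | 0.03 | 429 |
| 11.5% | 100% | 34.5 | 0.82 | 261 |

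Loss works in the same direction. If 10% of participants contributed nothing, 80% detection would give 300 × 0.10 × 0.80 × 0.90 = 21.6 expected and P = 0.04. That overstates the effect, because someone lost after baseline still contributes the baseline round.

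**3. Cases in the sensitivity denominator.** Of 30 cancers, an assumed lung share of 70% gives 21, 50% gives 15 and 30% gives 9. The denominator reaches 30 only if every one of the 30 is lung.

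**4. Precision.** Exact (Clopper-Pearson) 95% intervals at an observed sensitivity of 80%:

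- 24 of 30: 61% to 92%
- 12 of 15: 52% to 96%
- 8 of 10: 44% to 98%

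There are two separate routes to 15 cases: a 10% frequency with half of the cancers lung, or an assumed 5% frequency counted over all sites (300 × 0.05 = 15). The two should not be merged. Together they would give 7.5.

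**5. Source of the 10%, set beside the eligibility criteria.** The Discussion's figure covers malignancies without restriction to smoking-associated sites, in critical leg ischaemia, found through symptom-driven work-up. The trial admits that group but adds milder PAD and AAA, and it excludes patients with signs suggestive of malignancy. Those features could make 10% too high. Against this, undiagnosed cancers in the source, the entry requirement of at least 30 pack-years and the two repeat rounds could make it too low.

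**The case against.** The strongest defence is that 10% can be read as a detected yield. The source figure is itself a count of diagnosed cancers, the plan rounds it down from 11.5%, and the sentence says the 30 includes repeat rounds. On that reading 30/0.10 is coherent. It is a reasonable reading, but the text calls the figure a prevalence in the studied population and does not state it. Nor would it remove the mismatch between all sites and lung only.

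Several stronger readings are tempting, and the document does not support them:

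- *The arithmetic is wrong.* It is not. The division is exact; what fails is the meaning given to its result. A 53% chance of reaching the target is simply what planning on an expected count gives.
- *The prevalence comes from a population the trial excludes.* Critical leg ischaemia is eligible. What the exclusions remove is the kind of patient, with suggestive symptoms, in whom the source's cancers were looked for.
- *The prevalence is too high.* The article itself says true occult prevalence could be higher, and at 11.5% with full detection the target would be met with probability 0.82. The direction of bias is not known.
- *The target requires a CTC sensitivity of 100%.* The 30 detected are those found by the whole programme, including LDCT, repeat LDCT for volume doubling time and whole-body imaging. CTC sensitivity could be well below 100% and 30 cancers still be found.
- *The absence of a loss allowance or a precision derivation is a defect.* A journal article may leave both to the full protocol.

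**Conclusion.** The point holds in a limited form. As worded, 300 participants give about 30 cancers expected to be present. At least 30 detected follows only from complete detection and retention, and then with a probability of just 0.53, or from a cumulative-yield meaning of 10% that is not stated. At assumed detection of 90% or 80%, 27 or 24 are expected.

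Separately, and without any assumption about detection, the 30 planned cancers and the lung-only denominator are different quantities. The primary estimate will rest on fewer than those 30 cases unless all are lung. How many fewer depends on a lung share that the article does not give; at an assumed half, the interval at 80% sensitivity widens from 61–92% to 52–96%.

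The provenance of the 10% is a limitation to disclose. It does not show that 300 is too few. The point should be corrected, but it does not call for a change in sample size.

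**What to change.** Keep 300 and rewrite the sample-size paragraph as an expected count. For example:

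> With 300 participants and an assumed cumulative frequency of smoking-associated cancer of 10% over three rounds, about 30 cancers are expected to be present (15 at 5%; 34 at 11.5%). At 10%, 27 would be expected to be detected if the programme finds 90% of them and 24 if it finds 80%. The 10% is informed by a source in critical leg ischaemia with symptom-driven work-up, which differs from this cohort; the direction of any bias is uncertain. At an observed sensitivity of 80%, the exact 95% confidence interval would be 61–92% with 30 cases and 52–96% with 15.

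Then align the target condition of the sensitivity and specificity formulas with the primary objective, that is, smoking-associated cancers. Moving the sizing to lung cancer instead would take it away from the objective. If a lung-only analysis is kept, state its smaller expected case number and the lung share assumed.

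The cost is one reworded paragraph and an edit to the accuracy formulas, with no additional participants. The downside is that the stated yield and precision become less favourable.
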